## Abstract

**Background:**

Chronic Rhinosinusitis (CRS) affects approximately 1 in 10 UK adults and impacts quality of life quality of life significantly. Response to treatment may be driven by individual CRS endotypes and therefore work to delineate biomarker clusters that may separate responders from non-responders is needed. The ongoing MACRO three-arm parallel-group trial randomises adult CRS patients to endoscopic sinus surgery, macrolide therapy or placebo.

**Aim:**

This study aims to correlate CRS endotypes with clinical parameters from the ongoing MACRO trial, including olfactory function and outcomes in terms of response to treatment using core biomarkers sets.

**Methods:**

Adult CRS patients enrolled into the MACRO trial will be recruited from participating UK otorhinolaryngology departments. Nasal tissue samples and swabs will be obtained in theatre or clinic from patients randomised to all three trial arms. Nasal tissue will be analysed with multiplex electrochemiluminescence for 32 cytokines including IL-5, IL-13, IgE and periostin. Bacterial swabs will be analysed using illumina miSeq 16S amplicon sequencing. Mean expression for each biomarker will be reported for treatment responder and non-responder groups. Correlation of biomarkers with MACRO trial outcome data such as endoscopic evaluation scores and quality-of-life improvement scores will be reported.

**Discussion:**

Defining clear endotypes in CRS will contribute to refining patient pathways for the efficient use of clinical resources. This work may lay the groundwork for future studies to predict which patients might respond to medical or surgical therapy.

## Introduction

Chronic Rhinosinusitis (CRS) affects one in ten adults in the United Kingdom (UK) and impacts significantly on their quality of life [1]. Symptoms include a blocked and runny nose, loss of smell, facial pain, tiredness and worsening of breathing problems, such as asthma. Approximately 1% of UK adults receive treatment for CRS from their general practitioner (GP) each year, with a median of four GP visits. Traditionally, CRS has been dichotomised to two main phenotypes, based on endoscopic appearance of with (CRSwNP) or without nasal polyps (CRSsNP). Several biomarkers have been correlated to CRS phenotypes, such as nasal interleukin-5 (IL-5), IL-13 and periostin to CRSwNP [2, 3]. Furthermore, sinonasal bacteria such as *Staphylococcus aureus* have been implicated in the pathogenesis of CRS and treatments such as macrolide antibiotics have been shown to have immunomodulatory effects in selected patient groups [4].

More recently, a number of distinct CRS endotypes have been described, with incomplete overlap with the phenotypes above. Response to treatment may be driven by individual CRS endotypes [5] and therefore work to delineate key biomarker clusters that may separate responders from non-responders is needed. The relationship between disease severity, biomarkers and microbiome profiles is still unclear.

The ongoing MACRO three-arm parallel-group trial aims to establish best practice for the management of adults with CRS [6]. Recruitment began in autumn 2018 and to date over 350 patients have been randomised across 17 UK sites to receive either:

intranasal corticosteroids with saline irrigation plus endoscopic sinus surgery (ESS),intranasal corticosteroids with saline irrigation plus clarithromycin (250 mg twice daily for 2 weeks then once daily for 10 weeks), orintranasal corticosteroids with saline irrigation plus placebo.

The primary outcome measure for the MACRO trial is the sino-nasal outcome test-22 (SNOT-22) score at 6 months after randomisation. Secondary outcomes include the endoscopic Lund–Kennedy score, olfactory function measured using Sniffin’ Sticks, and health-care resource use. The parallel ExpRess study involves collection of nasal tissue samples and bacterial swabs from MACRO trial participants. The ExpRess study aims to correlate CRS endotypes with clinical parameters from the ongoing MACRO trial, including olfactory function and outcomes in terms of response to treatment using core biomarkers sets. This will further refine the biomarker sets that could be utilised in future clinical practice for personalised treatment for CRS.

## Methods

### Objectives

The ExpRess study is a multicentre prospective cohort study of adult patients with CRS recruited from at least five UK hospitals in parallel to the MACRO randomised controlled trial. Recruitment is currently ongoing at James Paget University Hospital, Norfolk and Norwich University Hospital, Guy’s and St Thomas’ NHS Foundation Trust, Imperial College Healthcare NHS Trust and Newcastle upon Tyne Hospitals NHS Foundation Trust. Study objectives include:

To quantify the cytokine expression pattern for MACRO trial participants,To determine if cytokine expression varies between treatment responder and non-responder groups,To identify if phenotypic characteristics collected from MACRO patients can be predicted by cytokine profiles,To define the bacterial profiles of MACRO trial participants.

### Participants

All participants are recruited from existing MACRO trial and are subject to the full eligibility criteria detailed in the MACRO protocol [6]. Selected eligibility criteria include:

Adults aged 18 and over with a minimum of 12 weeks’ history of inflammation of the nose and paranasal sinuses characterised by two or more symptoms, one of which should be either (1) nasal blockage, obstruction or congestion or (2) nasal discharge (anterior or posterior nasal drip). Other symptoms may include facial pain or pressure and reduction or loss of smell.Moderate or severe symptoms within the last 3 months with a SNOT-22 score ≥ 20.Symptom control not achieved following previous alternative medical therapy, including intranasal corticosteroids, short courses of antibiotics, or saline rinses, and therefore considered eligible for ESS.

Participants will be excluded if they meet any of the following criteria or those detailed in the full MACRO trial protocol:

Lund–Mackay non-contrast CT scan score < 4.Macrolide antibiotic treatment for >3 continuous weeks within the last 12 months.ESS in the previous 6 months or visible, open sinus cavities from previous surgery.Taking maintenance oral steroids or biologicsHas received systemic corticosteroids in the last one month.Rare or complex sinus conditions, such as CRS secondary to systemic disease (e.g. ciliary dyskinesias or granulomatous diseases) or suspected malignancy.Allergic fungal rhinosinusitis confirmed or suspected on CT imaging necessitating immediate surgery.Severe asthma (taking high doses of inhaled steroids, i.e. >1.5 mg per day).

All participants will have received nasal endoscopy within 3 months prior to recruitment to confirm CRS phenotype, and a non-contrast CT scan within 18 months prior to recruitment to confirm suitability for ESS.

### Recruitment

Participants will be recruited from January 2019 to September 2023 from participating UK sites. The recruitment target will be 120 patients in total across all three arms of the MACRO trial; equating to approximately 40 participants per arm. An a-priori sample size calculation was not possible due to lack of information around the baseline prevalence and variance of each cytokine included within the study groups and the likely difference between groups.

Patients will be approached for recruitment to ExpRess following randomisation to any of the three MACRO trial arms of surgery, macrolide antibiotics or placebo. Patients will be approached in clinic by the principal investigator or the research nurse and will be given a recruitment pack that will include a participant information sheet (S1 File) and consent forms. Following written informed consent, patients will have nasal tissue samples and endoscopically guided nasal swabs collected either at the point of randomisation or at their 6 month follow up visit. Participants randomised to the surgical arm of the MACRO trial are also eligible to have samples collected at the time of surgery instead, which is within 6 weeks of randomisation. This process is outlined in Fig 1.

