### Outcome measures

The primary outcome measure will be mean expression for each cytokine listed within a core set of biomarkers for treatment responder and non-responder groups. Responders will be defined as participants with a minimum 10-point improvement from their baseline SNOT-22 score at 6 months from randomisation to the MACRO trial. The cytokine data and microbiome profiles will be linked with the MACRO trial data from the Oxford Surgical Intervention Trials Unit following completion of the MACRO trial. MACRO data includes participant demographic information, disease-specific health-related quality of life using the SNOT-22 at 6 months, endoscopic Lund–Kennedy score, Lildholdt polyp grading score, health-related quality of life and quality-adjusted life-years using the SF-12v2 and EQ-5D-5 L questionnaires, olfactory function measured using Sniffin’ Sticks, and health-care resource use recorded using patient questionnaires.

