### Statistical analysis

Data will be analysed using RStudio version 1.2.13 software (RStudio, Massachusetts, United States). For continuous variables, results will be expressed as mean and standard deviation. Data distribution will be tested for normality using a Shapiro-Wilk test. If the variables are not normally distributed, the following statistical tests will be used: for dichotomous variables, a chi-square test will be used to determine difference between groups; while, for continuous variables, a Kruskal-Wallis test will be used for between-group comparison. If expression levels of biomarkers are below the detection limit, they will be replaced by the value 0 for analysis purposes. A p-value of <0.05 is considered significant.

For objective 1 the expression of each cytokine will be expressed as mean and standard deviation for participants from each MACRO trial arm. For objective 2 each MACRO trial arm will be analysed separately. Logistic regression analysis will be performed to determine the impact of cytokine expression levels on binary responder status (defined as a minimum 10-point improvement in baselines SNOT-22 score at 6 months). For objective 3 logistic regression analysis will be performed to determine the impact of cytokine expression levels on phenotypic characteristics such as the presence of nasal polyps or raised total serum IgE (>100 IU/ml). For objective 4 microbiome profiles will be reported as mean distribution of bacterial strains. Bacterial profiles will be compared alongside outcomes from the MACRO trial database using univariate and multivariate statistics, associating microbiome profiles to cytokine profiles and treatment success on included patients.

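### Tissue taken at randomisation and tissue taken at the 6-month outcome visit enter the same within-arm responder analysis, so a consequence of response can be reported as having an impact on it

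*Protocol article*

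**What the plan says.** **Sampling time.** Under Recruitment, participants in every arm have "nasal tissue samples and endoscopically guided nasal swabs collected either at the point of randomisation or at their 6 month follow up visit". Surgical-arm participants are "also eligible to have samples collected at the time of surgery instead, which is within 6 weeks of randomisation".

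**Outcome time.** Under Outcome measures, a responder is someone with a "minimum 10-point improvement from their baseline SNOT-22 score at 6 months from randomisation to the MACRO trial". The primary outcome is "mean expression for each cytokine listed within a core set of biomarkers for treatment responder and non-responder groups". No sampling time is attached to it.

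**Model.** Under Statistical analysis, "For objective 2 each MACRO trial arm will be analysed separately", and then: "Logistic regression analysis will be performed to determine the impact of cytokine expression levels on binary responder status". Arm is the only split named. No restriction, stratum or adjustment by sampling time is given. For objective 4, the same section relates microbiome profiles from the swabs to treatment success, again without reference to timing.

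**Intended use.** The Introduction presents the work as refining biomarker sets for personalised treatment. The Discussion describes it as groundwork for later studies that predict who responds to medical or surgical therapy.

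**The concern.** In the model, cytokine level is the explanatory variable and response is the outcome. That ordering suits a sample taken at randomisation. It does not suit a sample taken at the visit where response is scored. By then a clarithromycin patient has completed 2 + 10 = 12 weeks of a drug class that the Introduction credits with immunomodulatory effects, and a surgical patient has normally had the operation. Expression in such tissue may be a result of having responded.

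Analysing arms separately does not help, because both sampling times are allowed within every arm. At stake is the meaning of the primary outcome and objective 2: a responder versus non-responder difference could be a pre-treatment marker, a trace of recovery, or a mixture, and the analysis as described cannot tell which. The part of objective 4 that relates swabs to treatment success has the same weakness.

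**Working it through.** **Reproducing the plan's figure.** The only figure is the recruitment target: 120 / 3 = 40 per arm, as stated. The protocol says that no sample size calculation was possible, so there is no power figure to reproduce.

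**Inputs from the document.** About 40 per arm; significance at p < 0.05 (two-sided assumed); response at 6 months; both sampling times allowed in each arm.

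**Assumed inputs, not in the document.**
- Half the arm responds, giving 20 v 20.
- f is the share of the arm sampled at 6 months, taken as 1/3 or 1/2 and unrelated to response.
- d is the fall in expression, in SD units, found only in responders' 6-month samples, taken as 0.5 or 1.
- Pre-treatment expression is unrelated to response, so any significant result is false as a statement about pre-treatment markers.

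**Formulae, per cytokine.**
- Induced mean difference: Δ = f × d
- Responder variance after mixing: v = 1 + f(1 − f)d²; non-responder variance is 1
- SE = √[(v + 1)/20] and z = Δ/SE
- Rejection rate = P(Z > 1.96 − z) + P(Z < −1.96 − z)

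| d | f | Δ | v | SE | z | Rate (formula) | Rate (simulated t-test) |
|---|---|---|---|---|---|---|---|
| 0.5 | 1/3 | 0.167 | 1.056 | 0.321 | 0.52 | 8.2% | 8% |
| 0.5 | 1/2 | 0.250 | 1.063 | 0.321 | 0.78 | 12.2% | 12% |
| 1.0 | 1/3 | 0.333 | 1.222 | 0.333 | 1.00 | 17.0% | 16% |
| 1.0 | 1/2 | 0.500 | 1.250 | 0.335 | 1.49 | 32.0% | 31% |

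The simulated column used 20,000 data sets per scenario. A separate simulation of the logistic model (score test, 40 per arm, 8,000 runs) gave about 11% for d = 0.5 and 30% for d = 1.0 at f = 1/2. It gave about 5% at f = 0, as it should.

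**What drives the excess.** If the 6-month fall were the same in responders and non-responders, with sampling time unrelated to response, the two group means would stay equal and the rate would stay near 5%. The excess needs a change that differs by response.

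**Effect of separating the samples.** Restricting the logistic simulation to pre-treatment samples (f = 1/2, d = 0.8) returned the rate to 5.5%. The price is 40 × (1 − f) patients per arm: 30, 20 or 10 for f = 0.25, 0.50 or 0.75.

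**The case against.** The best defence has three parts.

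*The objective is only associational.* Objective 2 asks whether expression varies between responders and non-responders, and the aim is to correlate. A 6-month sample can describe that. This is fair as far as it goes, and it is why 6-month samples should be kept and reported. It does not rescue the mixture, because the model is worded in terms of impact and the Introduction and Discussion give the result a predictive use.

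*Pooling is never stated, and unseen material may separate the times.* The article does not say in words that samples from different times are combined. The flowchart is not shown, and a fuller analysis plan may exist. That stands as a caveat. Still, the sampling rule, the outcome time and the model are all stated, arm is named as a split, and sampling time is not.

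*The size is unknown.* This is correct. The percentages are illustrations.

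A reader might also infer more than the documents support:
- **Larger error rates from combining arms (60 v 60).** The primary outcome names no arm, but the stated objective 2 analysis is by arm, so figures for about 40 patients are the relevant ones.
- **Confounding because only surgical patients can be sampled in theatre.** Within an arm this link between arm and timing cannot create a responder difference. It affects comparisons across arms, such as the objective 1 means.
- **Any treatment effect on tissue is enough.** It is not; the change must differ by response.
- **Loss of the biopsy site after surgery, or selection of 6-month recruits on persisting symptoms.** The documents say neither.
- **The same restriction is needed for objective 3.** That objective concerns phenotype, such as polyps and serum IgE, not response, so the argument does not carry over.

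**Conclusion.** The concern holds for the primary outcome, objective 2 and the treatment-success part of objective 4. As written, samples that precede treatment and samples taken when response is scored enter one within-arm responder analysis, and the result is described as the impact of cytokines on response. This is a fault in the stated rules, not a detail left for later.

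The direction of the argument follows from the text; the size does not. With half of 40 patients responding and a third to a half sampled at 6 months, the false-positive rate per cytokine is about 8–12% for a 0.5 SD responder-specific fall and 16–31% for a 1 SD fall, against a nominal 5%. With few 6-month samples, or no response-specific tissue change, there would be little or no excess. The documents do not establish that any particular association will be false. They establish that the analysis could not distinguish a predictor from a consequence. This should be corrected before the biomarker data are linked to the trial outcomes.

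**What to change.** Amend Outcome measures and Statistical analysis as follows.

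1. Base the main responder analysis (primary outcome, objective 2 and the treatment-success part of objective 4) on samples taken at randomisation or, in the surgical arm, at surgery. Identify surgical samples as pre-surgery but up to 6 weeks after randomisation, since every arm also receives intranasal corticosteroids and saline, which may have been in use over that interval.
2. Analyse 6-month samples separately as post-treatment associations, without impact or predictive wording.
3. Report objective 1 results and sample counts by arm and sampling time.
4. For objective 3, keep all samples but report by sampling time.

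**Cost.** Provided sampling dates are recorded, this needs only changes of wording and no new data collection. The real cost is precision: the main responder analysis loses the 6-month samples, a fraction f of each arm. At f = 1/3 about 27 of 40 would remain (40 × 2/3) and at f = 1/2, 20. The actual loss is unknown until samples are counted by time, so that count should be made first, without reference to outcomes.

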**Fig 1 pone.0289407.g001:**
[figure not shown]
ExpRess study flowchart.

### Sample collection

Nasal tissue samples are collected by an otorhinolaryngologist either in clinic or in the operating theatre for participants randomised to ESS. Tissue is sampled during nasoendoscopy or ESS as a biopsy from the uncinate process of participants with CRS without nasal polyps (CRSsNP) or from nasal polyps for CRSwNP participants. Participants in clinic receive topical anaesthetic with 5% lidocaine and 0.5% phenylephrine up to five minutes prior to sample collection. Samples are stored in 2ml cryovials at -20°C at the collection site until transport to the Biorepository situated in Norwich Research Park at the University of East Anglia. Transport to the biorepository is assured by the local research teams and is performed in batches in a box filled with ice. After reception at the biorepository, samples are anonymised and stored at -80°C until analysis. Samples are pseudoanonymously linked to the MACRO trial database in Oxford.

Participants will also have endoscopically guided nasal swabs collected using DNA/RNA shield swabs (Cambridge Bioscience, Cambridge, UK). Nasal swabs for each participant will be taken from both the left and right middle meatus at a directional vector of 0–20 degrees in relation to the floor of the nose. Swabs will be stored at room temperature or colder and transported alongside nasal tissue samples to the Norwich Biorepository for storage at -80°C until analysis.

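### Biopsy site is fixed by polyp status, so the objective 3 polyp model cannot tell cytokine phenotype from tissue type

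*Protocol article*

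**What the plan says.** Sample collection: tissue is a "biopsy from the uncinate process of participants with CRS without nasal polyps (CRSsNP) or from nasal polyps for CRSwNP participants". No site sampled in both phenotypes is described.

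Objectives: the third objective is "To identify if phenotypic characteristics collected from MACRO patients can be predicted by cytokine profiles". Statistical analysis implements it as logistic regression for the "impact of cytokine expression levels on phenotypic characteristics such as the presence of nasal polyps", with raised total serum IgE as the other example.

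Outcome measures: the primary outcome is "mean expression for each cytokine listed within a core set of biomarkers for treatment responder and non-responder groups". A responder has a "minimum 10-point improvement from their baseline SNOT-22 score at 6 months from randomisation".

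Statistical analysis, objective 2: "For objective 2 each MACRO trial arm will be analysed separately", and "Logistic regression analysis will be performed to determine the impact of cytokine expression levels on binary responder status". No polyp or tissue-site term is named.

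The limitations in the Discussion cover the restricted cytokine panel, the missing early microbiome data and the absence of a sample size calculation. They do not mention tissue site.

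**The concern.** In the polyp model of objective 3, the outcome label decides which tissue supplies the predictor. Any cytokine that differs between polyp and uncinate tissue will appear to predict polyps, whatever the patient's endotype. The Introduction says that endotypes overlap only incompletely with the polyp phenotype. That is the distinction the study wants to draw, and for this outcome its sampling cannot draw it. At stake is whether a positive result can be read as phenotype prediction.

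There is a weaker, conditional risk for the responder comparisons. If polyp status happens to be related to response, a tissue-site marker could be labelled a response marker.

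**Working it through.** The article states no power, SD or effect size to reproduce. The only arithmetic it offers is 120 participants over three arms: 120/3 = 40 per arm.

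**Inputs from the article.** Site by phenotype (Sample collection); N = 120, about 40 per arm (Recruitment); significance at p < 0.05, taken as two-sided (Statistical analysis); 32 analytes (Abstract).

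**Assumptions, because the article gives no figures.** Site effect d in SD units; polyp share 30-70%; response 65% with polyps and 45% without.

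**Step 1: can site and polyp status be separated?** Code polyp status as 1/0 and site as 1 (polyp) or 0 (uncinate). The two columns are identical, so a design matrix with intercept, polyp status and site has rank 2 of 3. No covariate can separate them.

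**Step 2: apparent discrimination from site alone (objective 3).** With equal-variance normal distributions, AUC = Phi(d/sqrt 2).

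| d | d/sqrt 2 | AUC |
|---|---|---|
| 0.5 | 0.354 | 0.64 |
| 0.8 | 0.566 | 0.71 |
| 1.2 | 0.849 | 0.80 |

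**Step 3: chance of a significant result from site alone.** Using a two-mean comparison as an approximation to the single-cytokine logistic test, power = Phi(d / sqrt(1/n1 + 1/n0) - 1.96).

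- 60 v 60, d = 0.5: 0.5/0.1826 - 1.96 = 0.78, power 0.78.
- 36 v 84, d = 0.5: 0.5/0.1992 - 1.96 = 0.55, power 0.71.
- Over polyp shares of 30-70%: 0.24-0.28 for d = 0.25, and 0.98-0.99 for d = 0.8.

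This applies to each analyte that has such a site difference.

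**Step 4: leakage into the responder comparison (objective 2).** Suppose there is no true cytokine-response link and half the patients have polyps. Overall response is 0.5 x 0.65 + 0.5 x 0.45 = 0.55. The polyp share is 0.325/0.55 = 0.59 in responders and 0.175/0.45 = 0.39 in non-responders, a gap of 0.20. The spurious mean difference is gap x d: 0.16 SD for d = 0.8 and 0.24 SD for d = 1.2.

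Simulated logistic models at n = 40 (3,000 runs) reject in 6.3% (d = 0.8) and 9.0% (d = 1.2) of cases. A separate rerun gave 6-8%. With polyp status in the model the rate is 3-4%.

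**Step 5: sensitivity.** This used a t test and a linear model at n = 40, with 20 responders and 20 non-responders (4,000 runs).

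| Polyp share, responders v non-responders | d = 0.5 | d = 1.0 | d = 1.5 |
|---|---|---|---|
| 50% v 50% | 5% | 5% | 6% |
| 60% v 40% | 6% | 8% | 12% |
| 70% v 30% | 9% | 20% | 33% |

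Adjusted for polyp status, the rate is about 5% in every cell (4.5-5.7%).

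**The case against.** **The site effect is assumed.** The AUC figures only transform an assumed difference, so they illustrate and do not prove. This stands. The collinearity in step 1, however, needs no assumption.

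**An unseen analysis plan may contain the adjustment.** This is a condensed article, and a covariate list is ordinary analysis-plan detail. The article does not say that the objective 2 models are unadjusted, and polyp status is available for them: endoscopy confirms phenotype (Participants) and the Lildholdt grade is in the linked data (Outcome measures). This stands for objective 2 and is why that part is secondary. It does not help the polyp model, because no plan can separate two identical columns.

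**Adjustment may remove real signal.** If inflammation affects response partly through polyp disease, conditioning on polyp status takes out part of the effect of interest. This stands, and argues for showing both estimates.

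**Stronger readings that the article does not support.**

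- A reader might infer that the responder comparisons *are* confounded. That requires polyp status to be associated with response within an arm. The article says only that endotypes may drive response. With no association the error rate stays at about 5%.
- A reader might model all 120 patients together and find a false-positive rate of roughly 12-21% under the same assumptions. Objective 2 is analysed by arm, at about 40 patients, where the rate is 6-9%.
- A reader might reject the whole of objective 3. Raised serum IgE does not define the biopsy site. There, site is at most a confounder that polyp status can adjust for.

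**Conclusion.** The point holds for the polyp outcome of objective 3. Site is determined by polyp status, the model cannot attribute a cytokine difference to phenotype or endotype, and the limitations do not say so. The size depends on an unknown site effect: 0.5-1.2 SD gives an AUC of 0.64-0.80 from tissue type alone.

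For the primary outcome and objective 2, the conclusion is only that the comparisons may be confounded. With 65% v 45% response, half with polyps and a site effect of 0.8-1.2 SD, inflation at 40 per arm is modest (about 6-9% against 3-4% adjusted). It would be larger only with a stronger polyp-response association.

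This should be fixed, but it is not fatal. The study is a cohort offered as groundwork for later work, the polyp model is not its primary outcome, and the main remedy is a change of claim.

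**What to change.** 1. Restate the polyp part of objective 3 as a descriptive comparison of polyp tissue with uncinate tissue, and drop the prediction wording for that outcome.
2. Add the tie between site and phenotype to the limitations in the Discussion.
3. Make cytokine-phenotype prediction claims, such as for raised serum IgE, only within tissue type or adjusted for polyp status.
4. For the primary outcome and objective 2, report estimates adjusted for or stratified by polyp status beside the unadjusted ones. Site is constant within phenotype, so this removes the site artefact.

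Cost: rewording, plus a covariate that is already collected. No extra biopsy is needed. The price is a narrower objective 3 claim, one degree of freedom in each small per-arm model, and possible loss of signal that acts through polyp disease. Keeping the unadjusted estimates alongside makes that loss visible.
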